### Secondary endpoints

#### Clinical endpoints

##### Treatment failure

Treatment failure is defined as either failure to take up treatment or experiencing virological failure once taking treatment, namely:Not starting treatment within 6 months of the treatment recommendation.Not obtaining a viral load of < 50 copies/ml 6 months after commencing ART, or following viral suppression to < 50 copies/ml a viral load rebound to > 400 copies/ml on one occasion (single values > 50 copies/ml will be used rather than requiring confirmation because the number of viral load measurements during the 1 year follow-up are too few for confirmation to be possible).Following viral suppression to < 50 copies/ml, 2 consecutive viral loads > 50 copies/ml.

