### Participants

#### Inclusion and exclusion criteria

Participant inclusion criteria (Phases 1 and 2): (1) patients aged 18 years or above; (2) diagnosed HIV infection; (3) no previous prescription of ART (except women who have previously been prescribed ART for prevention of transmission during pregnancy and subsequently discontinued, who are considered eligible); (4) clinical recommendation to initiate ART treatment according to contemporaneous British HIV Association (BHIVA) guidelines or as deemed appropriate by the patient’s clinician; (5) able to provide written informed consent and available for long-term follow-up. Participant exclusion criteria: (1) patients who do not speak English; (2) those who plan to leave the country in the next 12 months and hence will not be available for follow-up appointments or telephone follow-ups; (3) participants already enrolled in a trial or in any research study which encourages adherence (e.g. clinical trial of an investigational medical product); (4) lack of capacity to provide informed consent; (5) hospitalisation for a mental disorder in the past 2 years; (6) current suicidality or self-harm; (7) pervasive developmental disorder; (8) active substance misuse/dependence in last 3 months which in the opinion of the physician or investigator renders the patient unable to adhere to the study protocol; (9) patients who have previously started antiretroviral therapy and subsequently discontinued, except if they have previously taken ART for pregnancy; (10) psychiatric or addictive disorders which in the opinion of the clinician or investigator could preclude obtaining informed consent.

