### Primary endpoint

#### The proportion of months under follow-up where adherence is greater than or equal to 90%

Adherence is defined by MEMS data. As the distribution of this variable is unknown, we will categorise the proportion of participants achieving ≥90% adherence as < vs ≥0.8 of the follow-up months. Essentially, this study assesses whether the participant has been ≥90% adherent for at least 80% of their time spent in the trial. The 80% threshold to define a good outcome is based on the fact that 4–6 weeks delay to ART initiation following a treatment recommendation is reasonable, and if followed by consistent ≥90% adherence to ART for the remainder of the trial (10 of the 12 months), the participant is likely to achieve and maintain viral load suppression. To calculate each monthly adherence value, the percentage of adherence (according to MEMS) for each individual over each month of follow-up from randomisation will be calculated, treating every day off ART or not taking all prescribed ART doses (indicating either nonadherence or delayed treatment initiation) as 0% adherence.

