### Statistical methods and analysis

The SUPA intervention is hypothesised to be superior to care as usual, and therefore the planned analysis is intention to treat, including all randomised participants, with all participants analysed according to the study group to which they were randomised regardless of subsequent treatment received. Primary analysis will include all randomised participants other than those randomised in error (defined as not intending to randomise the participant through e.g. miscommunication, rather than a participant or clinician decision once the allocation has been given).

A per-protocol analysis will be carried out on the primary endpoint including all participants in the intervention group who attended all 4 (2 + 1 + 1) sessions. If the intention to treat and per-protocol analyses on the primary endpoint leads to inconsistent results, then per-protocol analysis will also be carried out on all the other endpoints.

Continuous variables will be summarised by medians and IQRs or means and standard deviations as appropriate depending on the distribution, and compared between groups using ranksum tests or t-tests respectively. Comparisons of change from baseline in continuous variables will adjust for any baseline imbalances using either quantile or normal linear regression (depending on the shape of the distribution).

Categorical variables will be summarised by frequency tables, and compared between groups using chi-squared tests, unless any cell count is < 5 or cell percentage is < 5% in which case exact tests will be used. Binary variables will be summarised by percentages, using standard exact 95% CI for the risk differences. Time-to-event variables will be summarised using Kaplan-Meier curves and average differences between randomised groups estimated using Cox models. Patients without the event recorded will be censored at their last clinic visit. Proportionality of hazards will be tested; where significant departures exist, varying differences between randomised groups over time will be estimated using flexible parametric models of Royston and Parmar. Rate of treatment switching will be analysed using Poisson regression, including all changes to ART as events and the total time under follow-up through the earliest of 12 months or the last patient visit as the person-time at risk. Primary analysis will not stratify by clinical centre.

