### Strategies to promote recruitment

The following steps will be taken in order to achieve adequate participant enrolmentAn RA will attend multidisciplinary clinical meetings at each site in order to identify study eligible patients.Where possible an RA will be present at HIV clinics when ART-naïve patients have pre-booked appointments with a consultant and spoke with the consultant prior to the appointment in order to remind them of the patient’s eligibility for the trial. The RA will also attend emergency clinics in order to recruit patients attending clinics who are not on ART.Written information has been developed to inform patients about different types of research (e.g. observational studies and randomised controlled trials). This is intended to help patients to make an informed decision about whether to take part in each part of the study.

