## Discussion

We have described the design of the Supporting Uptake and Adherence to ART (SUPA) trial, an observational cohort study with nested randomised controlled trial evaluating the effectiveness of a CBT-based intervention to increase uptake and adherence to ART by addressing perceptual and practical barriers.

The intervention is based on the Necessity Concerns Framework and aims to address both perceptual and practical barriers to adherence as recommended by NICE [20] and BHIVA guidelines [9]. The intervention has been developed according to published guidelines for the development of complex interventions [15] and builds on preparatory research with PLWH showing that uptake and adherence to ART is driven by patients’ perceptions of their personal necessity for ART and concerns about adverse effects [18, 19]. To our knowledge, this is the first study to provide support at the time of a treatment recommendation to PLWH who may be at risk of delaying uptake or developing issues with adherence. This study targets individuals who may be considered as being hard to reach, and who are not usually represented in randomised trials. The study design allows the examination of process variables and the mechanism by which the intervention exerts its effect. The cost effectiveness analysis will enable health-care service providers to make informed decisions about the value of the intervention.

While it was not possible to mask the allocation of participants to intervention or control groups, we have taken steps to reduce bias, including blinding of the statistical team to group allocation and ensuring that data is not collected or entered by those delivering the intervention. It possible that the primary outcome measure (MEMS) may impact on adherence as it serves as a reminder to participants that they are monitored. However, the impact of adherence monitoring alone is likely to be minimal [36]. Although participants are selected for risk of delay to initiate treatment and nonadherence using a screening tool (BMQ-ART), patients who decline to take part in the study may represent a different group who are more at risk of disengaging from care. However, these participants will be followed up in the observational cohort, therefore their virological outcomes can be compared with those of trial participants.

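### The non-uptake part of treatment failure is timed from the treatment recommendation, not from randomisation, so a participant can already be a failure at entry

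*Protocol article*

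**What the plan says.** Under Treatment failure, the first way to fail is "Not starting treatment within 6 months of the treatment recommendation". The other ways are virological and concern participants who have started ART.

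Under Inclusion and exclusion criteria, entry requires a "clinical recommendation to initiate ART treatment according to contemporaneous British HIV Association (BHIVA) guidelines or as deemed appropriate" by the patient's clinician. No maximum time since that recommendation is given. Under Strategies to promote recruitment, one route is described thus: "The RA will also attend emergency clinics in order to recruit patients attending clinics who are not on ART".

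The primary endpoint uses a different time origin. Monthly adherence is computed "over each month of follow-up from randomisation", and days before ART is started score zero.

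Statistical methods and analysis gives general rules by type of variable. Binary variables get percentages and exact intervals for risk differences. Time-to-event variables get Kaplan-Meier curves, with "average differences between randomised groups estimated using Cox models" and the rule "Patients without the event recorded will be censored at their last clinic visit". The article does not say which type treatment failure is.

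**The concern.** A randomised comparison should count outcomes that arise after randomisation over the same window for everyone. Here the six-month window opens at an event that precedes randomisation by an interval that varies between participants and has no stated limit. Two consequences follow from the definition:

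- A participant advised seven months before entry and untreated is a failure on the day of randomisation. Starting ART the following week would not change that.
- A participant advised five months before entry has one month left, while one advised on the day of entry has six.

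Outcomes fixed before randomisation cannot respond to the intervention. They add the same expected number of failures to both arms and shrink the difference.

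The censoring rule raises a separate, conditional issue. Non-uptake is the absence of an event, so someone who never starts ART and stops attending at month 2 may have no failure recorded. If treatment failure is analysed as time-to-event, that person could be censored at month 2, although failing to take up treatment is what this component measures. Such loss is plausible, because the Setting section says sites were chosen for poor attendance after diagnosis.

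**Working it through.** **The plan's own figure.** Table 1 gives 186 per arm (372 in total) for 45% vs 60%, two-sided alpha 0.05 and 80% power. The two-proportion formula with continuity correction returns 183, 186, 183, 165 and 134 for the five rows, matching all of them. Those figures concern the primary endpoint and are not in dispute. The article gives none for treatment failure.

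**Step 1: the post-randomisation window.** If the recommendation precedes randomisation by *g* months, non-uptake failure falls 6 − *g* months after randomisation: 6 months for *g* = 0, 5 for *g* = 1, 3 for *g* = 3, 0 for *g* = 6, and 3 months before randomisation for *g* = 9. Counted from randomisation, it is 6 months for everyone.

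**Step 2: dilution (illustration).** From the documents: 186 per arm, alpha 0.05 two-sided. Assumed: non-uptake of 45% (control) and 30% (intervention) among participants not already failed, and a share *e* of each arm failed at entry. The 15-point gap borrows the primary endpoint's target difference. The observed proportion in an arm is *e* + (1 − *e*)*p*, so the difference is (1 − *e*) × 15 points. Power = Φ[(d − 1.96·SE₀)/SE₁], where SE₀ uses the pooled proportion and SE₁ the separate ones. The comparison is treated as binary and virological failure is left out.

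| Failed at entry | Control | Intervention | Difference (points) | Power |
|---|---|---|---|---|
| 0% | 45.0% | 30.0% | 15.0 | 85% |
| 5% | 47.75% | 33.5% | 14.25 | 80% |
| 10% | 50.5% | 37.0% | 13.5 | 75% |
| 20% | 56.0% | 44.0% | 12.0 | 64% |

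With 30% vs 15% assumed instead, power goes 94%, 88%, 81%, 67%.

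**Step 3: censoring (only if time-to-event).** Assume the same 45% vs 30%, failures falling at month 6, a share *s* of non-starters lost before then, and starters remaining under observation. The six-month Kaplan-Meier estimate is *p*(1 − *s*)/(1 − *ps*), against a true difference of 15 points.

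- *s* = 25% in both arms: 0.3375/0.8875 = 38.0% vs 0.225/0.925 = 24.3%, a difference of 13.7 points. About 105 of 140 failures are counted.
- *s* = 50% in both arms: 0.225/0.775 = 29.0% vs 0.15/0.85 = 17.6%, a difference of 11.4 points. About 70 of 140 are counted.
- *s* = 50% control, 25% intervention: 29.0% vs 24.3%, a difference of 4.7 points. About 84 of 140 are counted.
- *s* = 25% control, 50% intervention: 38.0% vs 17.6%, a difference of 20.4 points.

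Equal loss shrinks the difference. Unequal loss can move it either way.

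**The case against.** The strongest reply on the clock is that long gaps were not intended. The Discussion describes "support at the time of a treatment recommendation to PLWH". The 80% threshold of the primary endpoint is justified by a reasonable delay of four to six weeks after a recommendation, leaving 10 of 12 trial months, which presumes that recommendation and randomisation lie close together. The emergency-clinic route concerns patients not on ART and says nothing about how old their recommendation is. All of this stands against a stronger claim that a reader might infer, namely that some failures did precede randomisation. No section shows that anyone was enrolled long after being advised. It does not remove the point, because neither statement is an eligibility limit and the endpoint as defined allows such failures.

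A reader might also infer that pre-entry failures bias the result towards one arm. They do not: randomisation balances them in expectation.

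On censoring, a reader might conclude that disengaged non-starters are never counted. The article does not support that. The last-visit rule is general to time-to-event variables and treatment failure is not named as one. If it is analysed as binary, the issue falls away. The absence of a 12-month label in its heading makes the time-to-event reading plausible but not certain. Even then, the rule applies only where no event is recorded. Medical data come from patient notes and laboratory results, so non-uptake at six months could be recorded without attendance. The primary endpoint still scores untreated days as zero, and missed visits are an endpoint of their own.

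**Conclusion.** The clock point holds. The non-uptake component can include failures settled before randomisation and gives participants unequal time in which the intervention can act. The effect is dilution, not bias between arms. Its size depends on the interval from recommendation to randomisation, which the documents do not give. If gaps are short, the loss is close to nil; at an assumed 10% already failed at entry, 10 points of power are lost under the 45% vs 30% illustration.

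The censoring point is conditional. It needs a time-to-event analysis, a last clinic visit before the six-month mark and no failure recorded by other means. Bias between arms arises where loss among non-starters differs between them, and its direction depends on which arm loses more.

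Both points concern one component of one secondary endpoint. Every rate in the illustrations is an assumption. The sample size and the primary analysis are untouched.

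**What to change.** - **Clock.** For the trial analysis, run the six-month uptake window from randomisation for every participant. Report the recommendation-based definition as a sensitivity analysis.
- **Non-starters who are lost.** If a time-to-event analysis is used, do not censor at the last visit for the uptake component. Classify participants with no record of starting ART in the patient notes or pharmacy data as failures at six months, apart from documented transfers of care.
- **Sensitivity to that classification.** Add an analysis that treats participants lost before six months as missing or censored. The change of clock does not cover this. It is needed because the Data collection section promises refill data only up to the most recent clinic visit, so for someone who has left the clinic, no dispensing record may mean no information.

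The cost is wording and two sensitivity analyses on data already planned. Under Trial status, no cleaning or analysis had been done at submission, so the rules could be settled beforehand. The small downside is that some participants who moved without documentation and started ART elsewhere would be counted as failures; the last sensitivity analysis shows how much that matters.

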##### Disengagement from care at 12 months

Disengagement is defined as missing one or more routinely scheduled visits, including visits either not attended and not rescheduled or rescheduled but not attended before the participant’s next routine appointment is due.

##### Rate of ART regimen switches through 12 months

The total number of drug changes is calculated over the 12-month study period, including changing from one drug to another drug for any reason (excluding changes from 3TC to FTC and vice versa where these are simply due to changing a fixed dose combination tablet).

##### Referral out of the intervention at 12 months

This is defined as being referred out of the intervention for more specialist or intensive care (e.g. seeing a Psychiatrist or Clinical Psychologist for adherence issues). This information will be recorded in clinic notes and monitored by the research team.

#### Patient-reported endpoints

##### Changes in perceptions of ART between baseline and 12 months

Perceptions of ART will be measured using the BMQ-ART [16, 18] which was adapted following preparatory work with the target populations [23] to include items on culturally-specific and practical barriers specific to ART. The BMQ-ART includes 2 scales: the ART-Necessity scale and the ART-Concerns scale. The ART-Necessity scale consists of 10 items which assess how patients perceive their personal need for ART for keeping their HIV under control, maintaining their health and preventing illness. The ART-Concerns scale consists of 10 items measuring concerns about potential adverse effects of ART that have been identified in previous studies. These include fears about short- and long-term side effects, concerns about the timing of tablets and the disruptive effects of the ART regimen on daily life. Participants are asked to rate the extent to which they agree with each item on a scale with possible responses ranging from strongly agree (scored 5) to strongly disagree (scored 1). A total score for each scale is computed by adding the scores for each scale item together and dividing by the number of items. This yields a mean score ranging from 1 to 5 for the necessity and concerns scales.

##### Depression and anxiety at 12 months

The Hospital Anxiety and Depression Scale (HADS) [24] will be used to measure anxiety and depression. This 14-item measure was designed to detect the presence and severity of anxiety and depression among patients attending outpatient clinics without the possibility that scores would be contaminated by reporting of physical symptoms. Possible responses for each item ranged from 0 to 3, with each seven-item scale having a total possible score range of 0 to 21. Higher scores indicate greater anxiety or depression. Good psychometric properties of the HADS have been found in studies including medical outpatients [24, 25].

##### Health-related quality of life at 12 months

The Euroqol-5D (EQ-5D-5 L) is a self-completed measure of health-related quality of life (HRQoL), comprising 5 questions relating to dimensions of health: mobility, self-care, ability to undertake usual activities, pain/discomfort, and anxiety/depression [26]. Each dimension has 5 levels from ‘no problems’ (scored 1) to ‘extreme problems’ (scored 5). This results in a score on each dimension that can be combined to a 5-digit number describing the patient’s state of health. These health states will be combined with population weights to estimate individual utility scores ranging from 0 (worst health) to 1 (full health), required for generating quality-adjusted life years [27, 28]. The scale also includes a visual analogue scale (EQ-VAS) where the participant is required to indicate their level of health on a vertical scale with endpoints labelled ‘the best health you can imagine’ and ‘the worst health you can imagine’. This score (from 0 to 100) represents the patient’s judgement of their own health.

##### Health and social service use at 12 months

Health and social service utilisation will be collected at baseline and each follow-up using a modified version of the Client Service Receipt Inventory (CSRI) [29]. The CSRI is a widely used measure that can be adapted to meet the needs of each study/context in which it is used. It captures retrospective data on accommodation, employment (and time off work), contacts with community health professionals (e.g. GPs, social workers), hospital care (emergency department, inpatient and outpatient), laboratory tests, medication (including ART), social care and informal care from family and friends (i.e. support without payment). The CSRI enquires about whether contacts had occurred, how many, and where appropriate, the duration.

##### Symptoms attributed to having HIV and/or taking ART

Each participant’s experience of symptoms will be measured using the Symptoms Associated with HIV and ART Questionnaire (SAQ) [30]. The SAQ measure consists of 16 symptoms and a section where the participant is invited to add any symptoms that they are experiencing that are not listed. The participant answers by saying whether they experience each symptom or not (yes/no). Where the answer is ‘yes,’ the participant is asked to evaluate the severity of the symptom on a 5-point Likert-type scale with responses ranging from ‘very mild’ to ‘very severe.’ In addition, participants are asked to indicate whether they think the symptom is being caused by HIV, ART, both HIV and ART or neither. Scores will be generated for the total number of symptoms the participant is experiencing (possible range 0–16), the number of symptoms that the participant attributes to HIV (possible range 0–16), and the number of symptoms that the participant attributes to ART side effects (possible range 0–16).

